## **Fibre + statins phase**

### **Visit S12 (Day 84 ± 3)**

The participants will go to the hospital for a visit addressing the following aspects:

➤ *Clinical*

Identify the presence of clinical problems, concomitant treatments, etc.

Collection of adverse events.

Blood pressure and weight will be taken.

➤ *Analytical*

A request for two analyses will be issued. For the blood extractions, the patient will go to the hospital during the week prior to visit S16 on two occasions, with a 3- or 4-day interval between them, and the last extraction will be performed at most 3 days before the following visit. In this way, the investigator will have both results, particularly for the lipid profile, at the S16 visit.

Only the lipid profile will be determined at the first extraction. At the second extraction, and besides the lipid profile, the same biochemistry and haematological parameters as at visit S0 will be requested. Genetic polymorphisms will not be determined.

➤ *Dietary*

The patient will return the 3-day record and will be given a new one to complete.

➤ *Medication*

Evaluate compliance with treatment with fibre + statin. The patient should return used and unused medication containers.

The investigator will issue medication for the 4 remaining weeks of the study.

### **Visit S16 (Day 112 ± 3)**

The participants will go to the Hospital for the final visit of this second period, addressing the following aspects:

➤ *Clinical*

A clinical history similar to that of S0 will be made.

Identify the presence of clinical problems, concomitant treatments, etc.

Collection of adverse events.

Blood pressure and weight will be taken.

➤ *Analytical*

The results of the mean LDL-C value obtained in the two analyses made in the previous week (S15) will be noted at this visit S16. Similarly, the values obtained in the analyses on the last day of S15 will be noted as final parameters of the biochemistry and haematological trial.

➤ *Dietary*

The patient will return the 3-day record.

➤ *Medication*

Evaluate compliance with treatment with fibre + statin. The patient should return used and unused medication containers.

### **8.3. Methodology**

#### **8.3.1. Laboratory analysis**

The biochemistry analyses and haemogram will be carried out at each centre, barring the lipid profile, which will be conducted twofold, i.e. it will be determined in each centre so as to have the results in a few days and enable the investigator to take the relevant decisions at each point in the trial (inclusion criteria, continue or not at S8). Moreover, the determination of all samples will be centralised so as to minimise variability between centres and between analytical techniques.

The analysis of genetic polymorphisms will be centralised.

The trial central laboratory will be in the Hospital Universitario San Joan de Reus.

For these centralised determinations to be conducted, the samples should be stored frozen (–20°C) and sent to the central laboratory in accordance with the procedure explained in Annex 8.

➤ ***Cholesterol and triglycerides:***

They will be determined by means of an enzymatic colorimetric reaction adapted to a centrifugal autoanalyser.

➤ ***. HDL cholesterol:***

A polyethylene glycol solution will be used, precipitating the lipoproteins containing the apolipoprotein B (LDL and VLDL), making it possible to recover total HDL in the supernatant.

➤ **. LDL Cholesterol:**

It will be calculated by means of the Friedewald's formula:

$$c\text{-LDL}(\text{mg/dl}) = \text{total cholesterol} - \text{HDL-C} - (\text{triglycerides}/5)$$

➤ **. Vitamins A, E and C**

They will be determined by high performance liquid chromatography (HPLC) following a specific treatment depending on whether they are liposoluble (A and E) or hydrosoluble (C).

➤ **. Minerals**

They will be determined by colorimetry (Fe, Ca) or atomic absorption spectrophotometry (mg).

➤ **. Biochemistry and haemogram**

They will be determined by means of an autoanalyser.

➤ ***In vivo* study of the cholesterol-lowering, antioxidant, anti-inflammatory and antithrombotic activity**

Obtaining of the sample:

All patients will have 20 ml of blood extracted into EDTA plasma tubes (1 mg/ml). Immediately after extraction, it will be centrifuged at 1000 g at 4°C. The plasma will be separated and 10 µM of BHT will be added in order to protect the sample from lipid peroxidation. The plasma will be aliquoted and stored at -20°C for later analysis of the oxidative parameters (period of no more than 6 months). A fresh aliquot of plasma will be used for the determination of the biochemistry profile.

In Oxidation and antioxidant markers :

Determination of vitamin E: The vitamin E content (α-tocopherol, γ-tocopherol) in plasma and LDL will be determined using high resolution liquid chromatography (HPLC; Hewlet Packard 1050). Briefly, the internal standard (50 mg/l of tocopherol acetate) in ethanol will be added to 100 µl of sample (plasma EDTA, 10µM BHT) and after the precipitation of the proteins the lipids will be extracted with n-hexane. Immediately before injecting the sample into the HPLC, the lipid residue will be reconstituted in 100 µl of ethanol. The mobile phase is methanol (100%); the column used is Spherisorb-ODS 2, 125 × 4mm, Ø5 µ and the detection of α-tocopherol and γ-tocopherol is carried out at 292 nm. The concentration is determined extrapolating the results of the sample to a standard curve of known concentrations (1-25 mg/l) and correcting the loss of vitamin due to the process of extraction by the internal standard. The plasma vitamin E concentrations are expressed in mg/l.

The kinetics of oxidation (conjugated dienes) of the plasma lipoproteins LDL and HDL will be determined monitoring the change in absorbance at 234 nm at 30°C with a UV spectrophotometer (Kontron) in the presence of 6.7µM Cu++.

The determination of oxidated LDL in plasma will be done by an ELISA procedure using the murine monoclonal antibody mAB-4E6 as capturing antibody and an antibody against the oxidated Apo B joined to the peroxidase in solid phase. The coefficients of variation intra- and inter-trial for the methodology are: 2.8 % and 7.3 %, respectively.

The lipid peroxides in plasma will be measured using the generation of adducts of malondialdehyde-thiobarbiturate at 532 nm, expressed as equivalents of malondialdehyde, after lipid extraction with chloroform-methanol. The coefficients of variation intra- and inter-trial for the methodology are: 4.2% and 6.8 %, respectively.

In plasma, the concentrations of total cholesterol, LDL, HDL and triglycerides, apolipoproteins A and B, and lipoprotein (a) will be determined using the standard test and autoanalyser.

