## **Safety**

### ***What are the adverse effects of the intake of soluble fibre?***

Alterations of bowel movement such as flatulence and abdominal distension may present with the intake of soluble fibre at the beginning of treatment, but will disappear after a few days of follow-up.

The interaction between soluble fibre and the absorption of liposoluble vitamins and minerals must be recorded, although in most studies no changes have been detected between the group of patients taking soluble fibre and placebo consumers.

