#### **8.1.2. Secondary endpoints:**

The secondary endpoints are:

The effect will be analysed of the soluble fibre and consuming soluble fibre and a statin on:

- *The total cholesterol, the triglycerides, the HDL cholesterol, the apolipoproteins (apo) B-100 and A-1 and the lipoprotein (a).*
- *The oxidation markers: alpha tocopherol and gamma tocopherol in LDL, resistance of LDL to oxidation (lag time), LDL oxidation "in vivo" and lipid lipoperoxides.*
- *The inflammation markers: IL-1beta, interleukin-6, TNF-alpha, amyloid-A, high sensitivity C-reactive protein, fibrinogen, leukocytes.*
- *The indicators of antithrombotic activity: folic acid, homocysteine, plasminogen activator inhibitor (PAI-1).*
- *The individual response to the plasma lipids and their modulation by apolipoprotein E polymorphisms, cholesterol ester transport protein (CETP), apolipoprotein A-V, FABP 2, ABCG5 and ABCG8, fibrinogen, fibrinogen activator inhibitor, angiotensin converting enzyme and other polymorphisms which might describe their involvement in the development of cardiovascular diseases.*
- *Fasting complement component 3 (C3)*

- Mannose-binding lectin (MBL) activity
- Remnant-like particle cholesterol concentration (RLP-C)
- Parameters of cholesterol absorption and synthesis: plant sterols (campesterol and beta-sitosterol, reflecting cholesterol absorption) and lathosterol (reflecting cholesterol synthesis)
  - Determination of atherogenic apo B-containing particles (VLDL, IDL and LDL subclasses),
- HDL particle phenotype and HDL particle composition
- Cholesterol ester transfer protein activity

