| $e_{it}$                | indicates residual error, where $e_{it} \sim N(0, \sigma_e^2)$                                                                               |

In order to study other variables at other post-baseline visits, when necessary, an ANCOVA model will be made for each one, analogous to that described above. The baseline homogeneity will be evaluated using a Student's *t* test for independent data.

The variation in the LDL-C concentrations for week 8 to week 16, will be measured by way of intragroup analysis using analysis methods for repeat measurements.

The level of statistical significance will be established at 0.05 bilateral.

The evaluation of the continuous secondary efficacy endpoints will be analogous with the previously described ANCOVA for the primary endpoint. The continuous secondary endpoints to be analysed are described below:

- Weight and blood pressure
- Total cholesterol, triglycerides, HDL cholesterol, apolipoproteins (apo) B-100 and A-1 and lipoprotein (a).
- The oxidation markers: alpha tocopherol and gamma tocopherol in LDL, resistance of LDL to oxidation (lag time), LDL oxidation "in vivo" and lipid lipoperoxides.
- The inflammation markers: IL-1beta, interleukin-6, TNF-alpha, amyloid-A, high sensitivity C-reactive protein, fibrinogen, leukocytes.

- The indicators of antithrombotic activity: folic acid, homocysteine, plasminogen activator inhibitor (PAI-1).
- The individual response to the plasma lipids and their modulation by apolipoprotein E polymorphisms, cholesterol ester transport protein (CETP), apolipoprotein A-V, FABP 2, ABCG5 and ABCG8, fibrinogen, fibrinogen activator inhibitor, angiotensin converting enzyme and other polymorphisms which might describe their involvement in the development of cardiovascular diseases.
- Fasting complement component 3 (C3)
- Mannose-binding lectin (MBL) activity
- Remnant-like particle cholesterol concentration (RLP-C)
- Parameters of cholesterol absorption and synthesis: plant sterols (campesterol and beta-sitosterol, reflecting cholesterol absorption) and lathosterol (reflecting cholesterol synthesis)
- Determination of atherogenic apo B-containing particles (VLDL, IDL and LDL subclasses),
- HDL particle phenotype and HDL particle composition
- Cholesterol ester transfer protein activity

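### Plasma vitamin E, oxidised LDL and lipid peroxides have no lipid denominator, so the intended LDL-C fall can lower them with no change in oxidation or vitamin absorption

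*Protocol*

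**What the plan says.** **Units and matrices (Protocol 8.3.1, oxidation and antioxidant markers).**

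- Vitamin E: "The vitamin E content (α-tocopherol, γ-tocopherol) in plasma and LDL will be determined using high resolution liquid chromatography". For the plasma value the unit is fixed: "The plasma vitamin E concentrations are expressed in mg/l". No unit is given for the LDL content.
- Oxidised LDL: "The determination of oxidated LDL in plasma will be done by an ELISA procedure". The second antibody is directed at oxidised apo B. No unit and no ratio are given. This assay is the evident source of the listed endpoint on LDL oxidation in vivo.
- Lipid peroxides: "The lipid peroxides in plasma will be measured using the generation of adducts of malondialdehyde-thiobarbiturate at 532 nm". They are reported as malondialdehyde equivalents, with no lipid denominator.

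**Analysis (12.3.1).** "The evaluation of the continuous secondary efficacy endpoints will be analogous with the previously described ANCOVA for the primary endpoint". That model contains treatment and the variable's own baseline and nothing else. The section also allows an analogous model for other variables and visits where needed.

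**What the endpoint list names (8.1.2, repeated in 12.3.1).** The tocopherol and kinetic entries read "alpha tocopherol and gamma tocopherol in LDL, resistance of LDL to oxidation (lag time". The list also contains in vivo LDL oxidation and lipid peroxides.

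**Safety background (4.1).** "The interaction between soluble fibre and the absorption of liposoluble vitamins and minerals must be recorded".

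**The concern.** The oxidised-LDL assay responds to oxidised apo B, so its plasma reading depends on how many apo B particles are present as well as on how oxidised each one is. Tocopherol is measured in LDL as well as in plasma, and lipid peroxides are measured after lipid extraction, so both plasma values can also follow the amount of circulating lipid. The treatment is meant to reduce that amount. If it succeeds, these three values can fall in the fibre arm with nothing changed per particle, and the planned model has no term to separate the two explanations.

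Two readings would then be open to error. A lower plasma oxidised LDL or lipid peroxide value could be presented as an antioxidant benefit when it only restates the primary result. A lower plasma vitamin E in mg/l could be read as impaired absorption of a fat-soluble vitamin, which is the question that 4.1 wants recorded, when it only follows the lipid fall.

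**Working it through.** **Inputs from the protocol (6.3).** LDL-C difference 7.5 mg/dl at a baseline of 150 mg/dl; SD of change 20 mg/dl; two-sided alpha 0.05; power 80%; 112 evaluable per group. Statin phase: LDL-C from 157 to 125.6 mg/dl with fibre and from 161 to 136.85 mg/dl with placebo; 111 placebo and 98 fibre patients.

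**Inputs not in the documents (assumed, shown as ranges).** The share f of the marker carried in LDL: 0.5 to 1. The SD of the marker's change: 10% to 30% of baseline.

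**Step 1: the protocol's own figure.** n = 2 × (1.96 + 0.8416)² × 20² / 7.5² = 111.6, so 112 per group. The stated figure is reproduced.

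**Step 2: expected LDL-C falls.**
- Week 8, between arms: 7.5/150 = 5%.
- Statin phase: 31.4/157 = 20% with fibre and 24.15/161 = 15% with placebo, again 5 points apart.

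**Step 3: passive marker difference.** If the content per LDL particle does not change, the marker difference is f × 5%: 5%, 3.75% or 2.5% for f = 1, 0.75 or 0.5.

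**Step 4: chance that this passive difference is significant at week 8.** With z = d / (SD × √(2/112)), the chance is Φ(z − 1.96); the opposite tail is negligible. Example: d = 5 and SD = 15 give a standard error of 2.00, z = 2.49 and Φ(0.53) = 0.70.

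| Share in LDL (f) | Passive difference | SD 10% | SD 15% | SD 20% | SD 30% |
|---|---|---|---|---|---|
| 1 | 5% | 0.96 | 0.70 | 0.46 | 0.24 |
| 0.75 | 3.75% | 0.80 | 0.46 | 0.29 | 0.15 |
| 0.5 | 2.5% | 0.46 | 0.24 | 0.15 | 0.09 |

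For scale, LDL-C itself has a planned SD of 20/150 = 13.3%. A marker wholly proportional to LDL-C with that SD would have a chance of 0.80, the same as the primary endpoint.

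In the statin phase, with 111 and 98 patients, f = 1 gives 0.67, 0.44 and 0.22 at SDs of 15%, 20% and 30%; f = 0.5 gives 0.22, 0.14 and 0.09.

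**Step 5: does a ratio remove it?** Set the marker to 100 and LDL-C to 150 at baseline.
- f = 1: the marker falls to 95 and LDL-C to 142.5. 100/150 = 95/142.5 = 0.667, so dividing by LDL-C removes the passive effect.
- f = 0.5: the marker falls only to 97.5. 97.5/142.5 = 0.684, a rise of 2.6%, so LDL-C over-corrects a marker carried partly elsewhere. Such a marker needs a wider denominator.
- Total cholesterol as denominator: at an assumed level of 210–250 mg/dl, with only LDL-C changing, it falls by 7.5/210 = 3.6% to 7.5/250 = 3.0%. For f = 0.5 the ratio then moves by 0.975/0.964 to 0.975/0.970, about +1.1% to +0.5%, against −2.5% for the absolute value. The passive effect is reduced but not wholly removed.

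**The case against.** The strongest reply is that the protocol already contains measures that do not share this weakness. The listed tocopherol endpoint is content in LDL, not plasma, and plasma vitamin E is not on the 12.3.1 list of continuous endpoints. Lag time is a kinetic measure and not a concentration. Absolute circulating oxidised LDL is a legitimate quantity in its own right. If it falls because LDL falls, a significant result is a true difference and not a false positive. The lipids are measured anyway, so a ratio could be formed later, and the analysis plan may already do so. These are secondary markers in a long list, in a trial that calls itself exploratory.

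Much of this stands. The issue is one of interpretation and not of error rate, which is why the absolute values should stay in the report. It does not dispose of the point. For oxidised LDL and lipid peroxides the protocol states the matrix and the model, and both feed listed endpoints. For plasma vitamin E it fixes the unit, and the safety background gives that value a use. A ratio chosen after the results are known carries less weight than one fixed in advance.

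A reader might also infer that the cholesterol-absorption and synthesis markers have the same fault. The documents do not support that. For "plant sterols (campesterol and beta-sitosterol, reflecting cholesterol absorption) and lathosterol (reflecting cholesterol synthesis") the protocol gives names only, with no assay, unit or denominator, so to call them absolute concentrations would be to argue from silence. The same applies to tocopherol content in LDL, whose unit is not stated.

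**Conclusion.** The point holds for three measures: plasma vitamin E, plasma oxidised LDL and plasma lipid peroxides. For these, the planned 5% LDL-C difference at week 8, and the 20% versus 15% falls in the statin phase, can produce lower values with no change in oxidation or vitamin absorption. The passive difference between arms would be about 2.5–5%. With 112 per arm and SDs of 15–30%, the chance of a significant result at week 8 is about 24–70% if the marker is fully proportional to LDL-C and about 9–24% if half is carried in LDL. These figures rest on an assumed carrier share, an assumed SD and unchanged content per particle.

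It would be too strong to say that the LDL-C fall will show up in these markers: over much of the assumed range it would more often be missed than detected. The point does not extend to lag time, to tocopherol content in LDL, or to the plant sterols and lathosterol. No sample size depends on it, and the primary endpoint is unaffected. It is a low-priority improvement.

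**What to change.** In 8.3.1 and 12.3.1, prespecify for the same sample:

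- oxidised LDL per apo B (or per LDL-C);
- plasma alpha- and gamma-tocopherol, and lipid peroxides, per total cholesterol (or per cholesterol plus triglycerides).

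Report each ratio beside the absolute value, and state that any claim about oxidation or vitamin absorption rests on the ratio.

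The cost is one division per value and two reported forms of each marker. No new assay is needed: 8.3.1 already has total cholesterol, triglycerides, LDL-C and apo B determined in plasma. Annex 1 places the lipid profile and the vitamins at the same draws (D-7, the second S7 draw and the second S15 draw). Because baseline and final LDL-C are means of two draws, the text should say that the denominator is the value from the marker's own sample. The sample size does not change.

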#### Inflammation markers:

*The plasma concentrations of IL-1beta, interleukin-6, TNF-alpha, amyloid-A, C-reactive protein, fibrinogen will be determined using commercial ELISA kits (Amersham). The leukocyte concentration will be determined using automatic autoanalyser.*

#### Indicators of antithrombotic activity:

The plasma concentrations of folic acid, homocysteine, plasminogen activator inhibitor (PAI-1) will be determined using commercial ELISA kits (Amersham).

#### ➤ **Determination of the polymorphisms of the genes which predispose to cardiovascular diseases.**

##### Extraction of DNA:

The obtaining of genome DNA from each subject will be carried out using the cell package according to the protocol described in the commercial kit (Servicios Hospitalarios [Hospital Services], Spain).

##### Detection of the polymorphisms of the Apolipoprotein E (ApoE), angiotensin-converting enzyme (ACE), plasminogen activator inhibitor-1 (PAI-1) and fibrinogen genes:

A region which contains the described polymorphisms of the Apo E (E3/E3, E3/E4 and E4/E4), ACE (insertion/deletion (I/D)), PAI-1 (4G/5G promoter) and fibrinogen(-455G/A) genes will be amplified by PCR. The presence of the genetic variation will be evaluated using enzyme restriction.

### **8.3.2. Diet analysis**

The participants will be advised to follow a diet according to the recommendations for the prevention and treatment of cardiovascular diseases. Polyunsaturated fatty acids will account for less than 7% and the rest will be provided by monounsaturated fatty acids. Cholesterol intake will be lower than 200 mg daily.

The percentage of saturated fatty acids during the selection period (S-2 to S0), will be a maximum of 12%. Once the patient is randomised (after S0), the percentage of saturated fatty acids should be  $\leq 7\%$ .

Simultaneously, the intake of carbohydrates will be 55%, and proteins will provide approximately 15% of the remaining calories.

Alcohol intake will be lower than 30 g daily (equivalent to 1-3 glasses of wine or 1-3 beers or 1 standard measure of distilled drinks) and half for women.

The diets will be isocaloric and will be assigned according to needs, to maintain a stable participant weight.

To facilitate compliance with diet recommendations in participants from the different centres, the diet will be predefined in 7 levels of calories from 1600 Kcal to 3100 Kcal daily, to be able to adapt them to the energy needs of each participant. Similarly, cyclic 7-day menus will be made up, with a total of 14 meals, specifying the quantity of the different foods, as well as the diet characteristics. Each participant will be given their specific diet at an individual visit with the dietician.

In order to achieve maximum precision in the calculation of food intake, the volunteers will receive training on how to make measurements at home during the first interview with the dietician. The way the usual measures are assessed will be checked at the following visits to the dietician.

Compliance with the diet will be monitored by means of 3-day diet records and an interview with the dietician at the time of a medical visit. Furthermore, in the other weeks of the intervention period, the participants will be interviewed by telephone, without notice, for a 24h diet reminder (Annex 7).

Body weight will be monitored in parallel at each visit. If the participants' weight differs by more than 1 kg the calorie intake will be modified.

The participants will be encouraged to continue with their regular physical exercise and lifestyle during the study, and any change must be notified to the investigators.

The conversion of food into nutrients will be made using the French food composition tables (Répertoire général des aliments).

The procedure for the calculation, in the study Case Report Form, for the record of dietary and energy requirements, will be done as specified in Annex (16).

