#### | *Analytical*

The patient will be given the blood test request form for extractions on days D –10 ( $\pm 2$ ) and D –7 ( $\pm 2$ ). The mean lipid profile will be calculated from these two blood tests and will be used as the baseline LDL-C value. The results should be available to the investigator at visit S0 to confirm that the patient complies with the analytical inclusion criteria. The analyses on the D-7 will be taken as the baseline for general haematological and biochemistry parameters. The genetic polymorphisms of this sample will also be analysed.

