#### | *Dietary*

Each patient will be given a diet record for 3 days, two working days and one holiday, which they will complete and return at visit D-7. The patients will be instructed on how

to complete the record as precisely as possible, as indicated in the methodology section.

The patients will return the diet record on the day of the second analysis, i.e. D-7 ( $\pm 2$ ).

The dietician will have 7 – 10 days to analyse the data in the diet record and calculate patient energy requirements. He or she will thus be able to design the isocaloric diets for each case, which will be given to the patients at visit S0.

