### **12.3 Efficacy analysis**

#### **12.3.1 Primary efficacy analysis.**

The primary efficacy analysis will be conducted to evaluate the effect of the treatment with *Plantago ovata* husk versus placebo with regard to plasma LDL-C concentrations in patients with moderate hypercholesterolemia with low saturated fat diet.

The changes in the values of the plasma LDL-C concentrations will be evaluated by creating two endpoints:

- The primary analysis of the primary evaluation will be carried out with the total difference in the concentrations of LDL-C in plasma between visit S8 and visit S0 between both study groups.

- As additional sensitivity measure, the percentage of reduction of the concentrations of LDL-C in plasma between visit S8 and visit S0 between both study groups will also be evaluated.

The principal working hypothesis will be:

$$H_0: \Delta \text{LDL } \textit{plantago ovata} - \Delta \text{LDL placebo} < |7.5| \text{ mg/dl}$$

$$H_1: \Delta \text{LDL } \textit{plantago ovata} - \Delta \text{LDL placebo} \geq |7.5| \text{ mg/dl}$$

Where  $\Delta \text{LDL}$  = final LDL – baseline LDL

The statistical analysis will be carried out using a covariance analysis (ANCOVA) model with the baseline value as co-variable:

$$Y_{it} = \mu + Y_{it\text{BASELINE}} + T_t + e_{it}$$

where,

- |                         |                                                                                                                                              |
|-------------------------|----------------------------------------------------------------------------------------------------------------------------------------------|
| $Y_{it}$                | indicates the value of variable Y (difference in concentrations between visit S8 and visit S0) measured for patient I receiving treatment T. |
| $Y_{it\text{BASELINE}}$ | indicates the baseline value of the variable Y (difference in concentrations between visit S8 and visit S0) measured for patient I.          |
| $\mu$                   | indicates the overall average                                                                                                                |
| $T_t$                   | indicates the fixed effect of the treatment (T = 1 a 2)                                                                                      |

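### Baseline saturated-fat intake, recorded before randomisation, could be a second prespecified covariate in the primary ANCOVA for a small gain in precision

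*Protocol*

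**What the plan says.** Four places in the protocol bear on this point.

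- **Diet (8.3.2).** "The percentage of saturated fatty acids during the selection period (S-2 to S0), will be a maximum of 12" per cent. "Once the patient is randomised (after S0), the percentage of saturated fatty acids should be" 7% or less. The rule is the same in both arms.
- **Baseline LDL-C (8.2, Visit S-2, Analytical).** Blood is drawn on D-10 and D-7. "The mean lipid profile will be calculated from these two blood tests and will be used as the baseline LDL-C value". The individual diet is handed out at S0, after both samples.
- **Diet record (8.2, Visit S-2, Dietary).** "The patients will return the diet record on the day of the second analysis, i.e. D-7" (±2 days). The dietician then has 7 to 10 days "to analyse the data in the diet record and calculate patient energy requirements", so that the diet is ready for S0. Section 8.3.2 provides for foods to be converted to nutrients, and section 6.4 already uses saturated fat as a share of energy in a withdrawal criterion.
- **Primary model (12.3.1).** The S8-S0 difference is analysed by a "covariance analysis (ANCOVA) model with the baseline value as co-variable". The equation has an overall mean, the baseline value, treatment and error. No diet variable appears there, among the regression covariates in 12.3.2, or in the S0 comparability list in 12.2.

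**The concern.** The diet is tightened on the day treatment starts, after the baseline LDL-C samples. Section 4.1 treats a reduction in saturated fat as a means of lowering LDL-C. The S8-S0 change in each patient can therefore contain a diet component as well as a fibre or placebo component. Its size depends on how far that patient has to come down: a patient already at 7% has nothing to reduce, while a patient at 12% has 5 points.

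That patient-specific part is predictable in some degree from a measurement taken before randomisation. If the measurement is left out of the model, the variation it could explain stays in the residual, and a chance imbalance in starting diet is not adjusted for. At stake is some precision on the primary endpoint.

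**Working it through.** **1. The plan's own figure.** Section 6.3 gives a difference of 7.5 mg/dl, an SD of change of 20 mg/dl, two-sided alpha 0.05 and power 80%. The two-sample formula returns 112 per group, as stated. Power at 112 per group is 80.1%.

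**2. What a common diet fall does.** A fall shared by all patients goes into the intercept. Simulation with 112 per arm, 2,000 runs and a true effect of -7.5 mg/dl:

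| Common fall (mg/dl) | Mean estimate | SE of treatment effect | Residual SD |
|---|---|---|---|
| 0 | -7.42 | 2.67 | 19.96 |
| 8 | -7.42 | 2.67 | 19.95 |
| 20 | -7.39 | 2.66 | 19.98 |

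The estimate, its standard error and the residual SD do not respond to the size of the common fall. Only the variation between patients in the diet response is residual.

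**3. How much of that variation the covariate could explain.** The documents give none of the three inputs needed, so these are assumptions:

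- slope b: 1 to 2 mg/dl of LDL-C per 1% of energy (mid 1.5)
- between-patient SD s of saturated fat: 1 to 3 points (mid 2)
- reliability r of a 3-day record: 0.5 to 0.8 (mid 0.65)

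Share of variance explained: R² = (b × s)² × r / 20². Residual SD = 20 × √(1 − R²). Worth in patients = 290 × (1/(1 − R²) − 1).

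| | R² | Residual SD | Worth, of 290 | Power at 112 per group |
|---|---|---|---|---|
| Low: (1 × 1)² × 0.5 / 400 | 0.00125 | 19.99 | 0.4 | 80.2% |
| Mid: (1.5 × 2)² × 0.65 / 400 | 0.0146 | 19.85 | 4.3 | 80.7% |
| High: (2 × 3)² × 0.8 / 400 | 0.072 | 19.27 | 22.5 | 83.0% |

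**4. How the 12% ceiling limits the spread.** If every reduction lay between 0 and 5 points, the SD could not exceed 2.5, and a uniform spread from 7% to 12% would give 5/√12 = 1.44. At s = 1.44 with the same slopes and reliabilities, R² is 0.3% to 1.7%, worth about 1 to 5 patients. An SD of 3 requires starting intakes outside that band.

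**5. Chance imbalance.** The SE of the between-arm difference in baseline intake is s × √(2/112) = 0.134 × s. At 1.96 SE this is 0.26 points for s = 1 and 0.79 points for s = 3. Multiplied by the slope, the unadjusted contrast would move by 1 × 0.26 = 0.3 mg/dl up to 2 × 0.79 = 1.6 mg/dl, or about 3% to 21% of 7.5 mg/dl. This is part of the ordinary sampling error of the unadjusted estimate, not an addition to it.

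**The case against.** The strongest objection is that nothing here is wrong in the plan. The diet rule is the same in both randomised, double-blind arms. Baseline LDL-C is already in the model. Age, sex, BMI, centre or genotype could be proposed on the same general grounds. This stands, so the point can only be an optional improvement. What sets this covariate apart is that the protocol changes the factor itself at S0, asserts its link to LDL-C, and measures it beforehand.

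Two further objections also stand. The size rests wholly on assumed inputs, and R² is set against the SD of the raw change, with no account of overlap with baseline LDL-C. And the covariate is a self-report that may be missing for some patients; without a rule, those patients would drop out of the intention-to-treat model, which could cancel a gain worth a few patients.

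The argument that the ceiling caps the spread stands only in part. The 12% limit is not among the selection criteria in 6.1 and 6.2, the diary instructions in Annex 6 ask patients not to change their eating habits, and the withdrawal threshold in 6.4 is 15%. Starting intakes above 12% are therefore possible, which is why the SD range runs to 3.

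A reader might infer three stronger things, and the documents support none of them:

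- *That the whole diet-driven fall sits in the error term.* The shared part is in the intercept, as step 2 shows.
- *That every patient changes diet at S0.* The 12% is a maximum, and patients at or below 7% need not reduce.
- *That the contrast is biased or the trial underpowered on this account.* Randomisation protects the contrast. The documents do not say whether the study behind the planning SD of 20 mg/dl had a similar diet step, so no shortfall in power can be derived.

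**Conclusion.** This is a small, cheap gain in precision and not an error. The design facts are confirmed: patients above 7% must reduce saturated fat from S0, baseline LDL-C precedes that change, starting intake is scheduled to be recorded and analysed before randomisation, and the written primary model does not use it.

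On the assumed inputs the covariate removes about 0.1% to 7% of residual variance. At mid values that is about 1.5%, equivalent to about 4 of 290 patients and 0.6 points of power (80.1% to 80.7%). The upper end needs a slope of 2, an SD of 3 points and a reliability of 0.8 together, and an SD of 3 is possible only if intakes range beyond 7% to 12%. The stated sample size and power are unaffected.

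**What to change.** In 12.3.1, add baseline saturated-fat intake (% of energy) as a second continuous covariate in the S8-S0 ANCOVA. Specify four things, before unblinding:

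- The value comes only from the 3-day record returned at D-7. Records returned from S4 onwards are post-randomisation and must not be used.
- Patients with a missing or unusable baseline record stay in the model by simple baseline imputation, for example the overall mean across both arms.
- The model with baseline LDL-C alone is kept as a sensitivity analysis.
- The LDL-C covariate is defined as the mean of D-10 and D-7. The present key to the equation describes it as the baseline of the S8-S0 difference, which does not exist before treatment.

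The cost is one degree of freedom, a few lines of text and the handling of any missing record. No new data collection is needed, because the record is already planned and analysed for the diet prescription.
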